### Methods in analysis to handle protocol non-adherence and any statistical methods to handle missing data {20c}

Since the linear mixed model includes all available data (i.e., T1, T2, T3, and T4), intention-to-treat analysis is possible without imputing data.

### Plans to give access to the full protocol, participant-level data and statistical code {31c}

The full protocol and anonymized participant-level datasets used and analyzed during the current study are available from the corresponding author upon reasonable request.

## Oversight and monitoring

### Composition of the coordinating center and trial steering committee {5d}

The exercise testing is performed at the research groups’ own clinical gym: “Rörelseglädjelabbet” at Karolinska University Hospital, Stockholm, Sweden, and at the Norwegian site at the research lab facilities at the Norwegian School of Sports Sciences, Oslo, Norway. Both sites have all the necessary equipment to carry out advanced exercise tests including measurements of body composition and muscle ultrasound, and both labs have the necessary safety equipment (defibrillator, hygiene liquid dispensers, balance railings) and are in close proximity to medical staff if required. The multi-professional competence of the researchers means that the team is well-qualified to collect and analyze all data.

An established and working relationship to support this project exists with the Upper Gastrointestinal Unit at Cancer Theme at Karolinska University Hospital and at Oslo University Hospital which will play a key role in the inclusion of patients for this project. A working relationship also exists with The Swedish School for Sports and Health Sciences and The Norwegian School of Sports and Health Sciences, which has long experience with obtaining muscle biopsies from both healthy and clinical populations and to perform biochemical analyses. All biochemical methods planned to be performed in this study are set-up in these labs.

### Composition of the data monitoring committee, its role, and reporting structure {21a}

Since this randomized controlled exercise trial is not considered to be a large, complex, or high-risk clinical trial, such as those involving new drugs or medical devices, we deem that a DMC is not needed.

### Adverse event reporting and harms {22}

All AEs related to exercise or study measurements are recorded and reported to the sponsor. Participants in both groups are asked by the study personnel about exercise- and study measurement-related AEs in a standardized manner during all follow-up visits. In addition, the weekly telephone calls/video calls that are made to monitor exercise adherence for participants allocated to the exercise group will also be used to ask whether any potentially exercise-related AEs occurred during or since the last exercise session.

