**Fig. 1 Fig1:**
[figure not shown]
Schedule of enrolment, interventions, and assessments in the PREV-Ex trial*. T0 diagnosis or post neoadjuvant chemotherapy; T0–T1 Prehabilitation period 1–4 weeks; *Surgery to discharge from hospital (2–3 weeks); T2–T3 post-surgery training period 5–6 weeks; T3–T4 follow-up 6 months following surgery

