Due to the COVID-19 pandemic, the study start was delayed for almost 1 year. The initial plan was to include a more homogenous group: patients diagnosed with pancreatic or biliary tract cancer undergoing a pancreaticoduodenectomy; however, there were major challenges with the inclusion rate resulting in the study taking longer and risking a loss of statistical power. Amendments were made to the original plan to expand the inclusion criteria to patients undergoing either pancreaticoduodenectomy or laparoscopic surgery and to also patients with malignancies in the liver amendable for surgical resection. These changes were approved by the Swedish Ethical Review Authority and the Norwegian Regional committees for medical and health research ethics. We are aware that this will result in a heterogeneous group of patients. There is considerably less risk of complications for patients undergoing laparoscopic surgery compared to a pancreaticoduodenectomy; however, these potential differences will be adjusted for in the statistical analysis. Moreover, time to surgery and post-surgery recovery are similar across the diagnoses. In this study, we decided to include any patient who is diagnosed with resectable pancreatic, biliary tract, or liver cancer regardless of time-to-surgery which means that some patients will only have time to perform (T0) before surgery, while some will perform both (T0) and (T1). In some cases, time-to-surgery is only a few days which means that inclusion is not possible at (T0) but will instead take place at (T2). The reason for including patients at (T2) is that time-to-surgery is significantly shorter at the Norwegian site; consequently, amendments to the original plan had to be made to accommodate for the reduced time-to-surgery. We will perform a subgroup analysis to evaluate the rehabilitation effect (T2 to T3). Other amendments to the original plan include the addition of digitally supervised exercise and an exercise diary to be able to monitor exercise adherence more efficiently.

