We anticipate that adaptations to the exercise program will be required since these patient populations have a high disease burden and fluctuating health and performance status. Regular monitoring of the patients’ health status will be performed to adapt and personalize the exercise prescription. This means that the prescribed cuff pressure may decrease based on the self-reported rating of perceived exertion and the exercises may vary slightly based on post-surgery restrictions or complications. We believe that such adaptations to the initial planned training schedule are necessary for these specific populations.

To enhance adherence to the exercise regimen, the exercise sessions are personalized and home-based to avoid travel which has been shown to be a major barrier to exercise [23]. Additionally, utilizing a home-based training approach could offer a safer alternative for these patient populations, given their heightened susceptibility to infections. It is imperative for them to steer clear of infections to ensure timely eligibility for surgery.

In exercise-oncology trials, contamination is reported in 37% of cases. To mitigate this risk, we have implemented recommended measures, such as offering general exercise guidance along with an activity tracker to the control group [24]. While providing the activity tracker may potentially increase the physical activity levels of controls, research indicates that such proactive measures reduce the likelihood of drop-out and contamination [24].

In conclusion, in the PREV-Ex exercise trial, we are investigating the effects of blood flow-restricted resistance training in patients with pancreatic, biliary tract, and liver cancer in the perioperative setting on muscle thickness and muscle cross-sectional area, physical fitness, body composition, patient-reported and objective health-related outcomes, hospitalization, blood status, and skeletal muscle molecular characteristics. Findings from the study will shed light on the potential of a personalized exercise approach to act as a powerful strategy to counteract cancer-related muscle wasting. It will pave the way for the evidence-based practice that is needed to embed exercise into routine care for patients that are in crucial need for a strategy that can slow down the rate of skeletal muscle deterioration.

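### An AE must be related to exercise or a study measurement to be recorded, and only the exercise arm is also asked weekly, so a by-arm count pooling both sources would lean upward there

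*Protocol article*

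**What the plan says.** Under Adverse event reporting and harms {22}, the protocol sets three rules.

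- **Scope:** "All AEs related to exercise or study measurements are recorded and reported to the sponsor".
- **Both arms, at all follow-up visits:** "Participants in both groups are asked by the study personnel about exercise- and study measurement-related AEs in a standardized manner".
- **Exercise arm only:** on the weekly adherence calls, staff also "ask whether any potentially exercise-related AEs occurred during or since the last exercise session".

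Other sections bear on these rules.

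- Intervention description {11a} sets remote supervision or calls at once a week, with 1–4 weeks of training before surgery and 5–6 weeks after it.
- Participant timeline {13} places assessments at T1, T2, T3 and T4. It allows some patients only T0 before surgery and lets others enter at T2. Hospitalization is read from medical records at T4.
- Who will be blinded {17a} states that participants, study nurses and investigators know the allocation.
- The Discussion says of the operations included: "There is considerably less risk of complications for patients undergoing laparoscopic surgery compared to a pancreaticoduodenectomy". It also says that "the exercises may vary slightly based on post-surgery restrictions or complications".
- The Discussion describes "offering general exercise guidance along with an activity tracker to the control group", so controls can also have exercise-related events.

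**The concern.** Two features of these rules weaken the harms data.

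**Attribution comes first.** An event is asked about, and recorded, if it is related to exercise or a measurement. After major abdominal surgery many events could be due to the operation, the disease or the training. Whoever decides, patient or staff, knows the allocation. An event put down to surgery falls outside the AE question in both arms. Yet the Background suggests that BFR-T might reduce AEs and improve surgical outcomes, and the Discussion treats complication risk as a known difference between the operations.

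**Questioning is unequal.** The exercise arm has an extra weekly route for reporting. If visit and call reports were added together and shown by arm, that arm would tend to show more exercise-related AEs even if the true rates were equal.

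At stake is how the harms data can be read, in a trial with no independent data monitoring committee. No efficacy estimate or test is affected.

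**Working it through.** The protocol gives no AE figure, so there is none to reproduce.

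**1. Occasions on which AEs are asked about.** Occasions = follow-up visits after entry + weekly calls (exercise arm only). Visits come from Participant timeline {13} and calls from Intervention description {11a}.

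| Patient | Control | Exercise | Ratio |
|---|---|---|---|
| Full course (T1–T4; 6–10 calls) | 4 | 4 + 6 to 4 + 10 = 10–14 | 2.5–3.5 |
| Only T0 before surgery (T2–T4; 5–6 calls after surgery, 0–1 assumed before) | 3 | 3 + 5 to 3 + 7 = 8–10 | 2.7–3.3 |
| T2 entrant (T3, T4; 5–6 calls) | 2 | 2 + 5 to 2 + 6 = 7–8 | 3.5–4.0 |

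If T4 is not a visit at which AEs are asked about, the counts are 9–13 against 3, 7–9 against 2, and 6–7 against 1.

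**2. What this could do to a pooled count.** More questions do not mean proportionally more events. Let q be the chance that an event is reported at a visit and w the chance that it is reported on a call, taken as independent. With equal true rates of exercise-related AEs:

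pooled ratio, exercise to control = [1 − (1 − w)(1 − q)] / q

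The protocol gives neither q nor w, so all values are assumptions.

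| | q = 0.5 | q = 0.7 | q = 0.9 |
|---|---|---|---|
| w = 0.7 | 1.70 | 1.30 | 1.08 |
| w = 0.9 | 1.90 | 1.39 | 1.10 |

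Letting both run from 0.3 to 0.9 gives 1.03 (q = 0.9, w = 0.3) to 3.1 (q = 0.3, w = 0.9). The ratio exceeds 1 unless visits capture every event (q = 1). The direction is therefore clear and the size is not known. Measurement-related AEs are not asked about on the calls and are unaffected.

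**3. Where a complication would be recorded.**

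- AE question: only if the event is attributed to exercise or a measurement.
- Hospitalization at T4: a complication that leads to readmission is caught.
- Index stay: the Fig. 1 legend puts surgery to discharge at 2–3 weeks for the trial's patients generally, so a hospitalization record does not show a complication within that stay. No section states another route.

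For scale, at an assumed complication rate of 20%, 30% or 50%, 52 × rate = 10.4, 15.6 or 26 patients would have one. The protocol gives no rate.

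**4. Choosing the remedy.**

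- Dropping every AE first heard on a call leaves the exercise arm with (1 − w)q / q = 1 − w of the control count, which is 0.30 at w = 0.7 and 0.10 at w = 0.9. That reverses the bias.
- Counting by the visit question, including events already mentioned on a call, gives q / q = 1.0 if calls do not change what patients say at visits.

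**5. What a comparison could show.** With 26 per arm and equal proportions p, the 95% half-width is 1.96 × √(2p(1 − p)/26), or 21.7, 24.9 and 27.2 percentage points at p = 0.2, 0.3 and 0.5.

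**The case against.** The case on the other side has four parts.

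- **No by-arm AE comparison is planned.** AEs are not a listed outcome, and the only between-arm event test is for hospitalization. A reader might infer that the trial's AE comparison is already inflated. The documents do not support that, because no such comparison is stated. The bias is conditional on someone pooling the two sources by arm. This stands.
- **Complications are not wholly lost.** A reader might infer that surgical complications go uncaptured. That goes too far. Readmissions are caught, Criteria for discontinuing {11b} considers SAEs and a worsening condition, and the Discussion promises regular monitoring of health status. The article does not say that other events go unrecorded in the full protocol. What remains is narrower: the stated AE rule covers related events, and index-stay complications have no stated route.
- **The weekly question is good safety practice.** Patients doing home BFR training should be asked about harm, and a question about the last session has no direct control equivalent. This stands, and the calls should stay. Stopping or changing training for one patient needs no comparison, and the visits give both arms a common source.
- **The magnitude is assumed.** Reporting rates, their independence, equal true rates and the complication rate are all assumptions. Equal true rates of exercise-related AEs may be unlikely when one arm has prescribed training. This also stands, so only the direction and the count of occasions should be relied on.

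These arguments do not remove the core. The relatedness condition and the exercise-only questioning are stated collection rules, not gaps left by a condensed article.

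**Conclusion.** The point holds in a limited form. As written, relatedness to exercise or measurements is the entry condition for recording an AE, judged with knowledge of allocation, and the exercise arm has extra weekly questioning. For a full-course patient that means 10–14 occasions against 4, which follows from the schedule if T4 counts as a visit.

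Any AE count pooling visit and call reports would be biased upward in the exercise arm. The amount is unknown: illustrative ratios run from 1.03 to 3.1 and rest wholly on assumed, independent reporting rates and equal true rates. Events attributed to surgery or disease fall outside the AE question in both arms, and index-stay complications have no stated route.

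No primary or secondary estimate, test or interim rule is affected. This is a cheap improvement of minor severity.

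**What to change.** 1. At the follow-up visits common to both arms, ask about any AE, and judge relatedness afterwards as a separate item.
2. In the T4 medical-record review already planned for both arms, also extract SAEs and postoperative complications from T0 (or T2 entry) to T4, whatever their attribution. Because the review is retrospective, it can also reach patients already enrolled.
3. Keep the weekly calls for safety. Add a source flag, and show AEs reported only on a call as description of the exercise arm.
4. Base any between-arm count on answers to the visit question, including events already mentioned on a call. Do not discard everything first heard on a call. Keep the comparison descriptive, given half-widths of about 22 to 27 points.

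The cost is a few fields in the record review, one reworded question and one flag on the AE form. No extra patients, visits, calls or committee are needed. The downside is more AEs to log, most of them unrelated to training.

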### Intervention description {11a}

#### Exercise intervention

The exercise intervention will consist of home-based low load blood flow restricted resistance training 4-5 times weekly during the 1–4-week prehabilitation period and 2–3 times per week during the 5–6-week rehabilitation period. During the initial baseline visit (T0), patients who are allocated to the exercise group will receive instructions about how to perform the BFR-T exercises. Blood flow restriction is induced by pressure cuffs connected to a tourniquet system (Occlude, Aarhus, Denmark). The cuff is wrapped around the proximal part of the legs and arms to partially restrict blood flow into the muscle and occlude blood flow out of the muscle and the cuff pressure will be set at 50% of arterial occlusion pressure (AOP). The individualized cuff pressure should not cause pain. During the preoperative phase, patients will perform three sets of 20–15–15 repetitions for each exercise during the first week and for the remaining pre-operative weeks the volume will be increased to three sets of 30–15–15 repetitions. During the rehabilitation phase post-surgery, three sets of 20/30–15–15 repetitions will be performed. During BFR-T, the cuff will be kept inflated and released immediately upon completion of the third set. The weight loads used during exercise will be very low using the individual’s own body weight and resistance bands will be used for two of the exercises. Exercises consist of a warmup (5 min walking with cuffs placed on the legs), lunges, squats, push-ups, seated row with a resistance band, and biceps curls with a resistance band. The exercises and the repetitions/sets will be adjusted according to the patient's functional capacity. The home-based sessions will be monitored/supervised digitally or through telephone calls once per week. The home-based exercise setup enables participants to avoid time-consuming travel and allows participants to exercise independently, without access to a gym facility. This may be especially important to consider during and after times of a pandemic considering that this patient population may be more sensitive to infections.

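### The weekly adverse event question in the exercise arm reaches back only to the latest session, although two to five sessions are scheduled per weekly contact

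*Protocol article*

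**What the plan says.** Three statements in the protocol article bear on this point.

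- **Training schedule** (Exercise intervention, under Intervention description {11a}): home-based sessions take place "4-5 times weekly during the 1–4-week prehabilitation period and 2–3 times per week during the 5–6-week rehabilitation period".
- **Contact schedule** (same section): "The home-based sessions will be monitored/supervised digitally or through telephone calls once per week".
- **Harms ascertainment** (Adverse event reporting and harms {22}): the section opens with "All AEs related to exercise or study measurements are recorded and reported to the sponsor". It then gives two routes. At visits, "Participants in both groups are asked by the study personnel about exercise- and study measurement-related AEs in a standardized manner during all follow-up visits", with no stated limit on how far back the question goes. In addition, "the weekly telephone calls/video calls that are made to monitor exercise adherence for participants allocated to the exercise group" are used to "ask whether any potentially exercise-related AEs occurred during or since the last exercise session".

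Two other places matter. Criteria for discontinuing or modifying allocated interventions {11b} makes the severity, frequency and relatedness of adverse events part of the decision to change or stop the intervention. The Discussion says that an exercise diary was added by amendment; its stated purpose is to monitor adherence, and no use for adverse events is mentioned.

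**The concern.** The contact interval is one week, but the question asked at that contact goes back only to the most recent session. Consecutive windows therefore do not join up. Suppose a participant has a short-lived event at Monday's session, trains again on Wednesday and Friday without trouble, and is called on Saturday. The Saturday question starts at Friday's session, and next week's call starts later still. No call asks about Monday.

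This sits badly with the section's own opening statement that all exercise-related events are recorded. It is a window that the article states, not a detail left to a fuller document.

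At stake is the completeness and timeliness of the harms record for home sessions. Events that come and go within a day or two are the ones a narrow window loses. They are also the ones least likely to be recalled accurately at a visit weeks later. Section {11b} relies on the frequency of events, and frequency cannot be judged promptly if many sessions are not asked about.

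**Working it through.** The protocol gives no figure for coverage, so there is nothing to reproduce. The check is a count.

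**Inputs**

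- Prehabilitation: "4-5 times weekly during the 1–4-week prehabilitation period", so *a* = 4 or 5 sessions a week for *p* = 1 to 4 weeks.
- Rehabilitation: "2–3 times per week during the 5–6-week rehabilitation period", so *b* = 2 or 3 sessions a week for *r* = 5 or 6 weeks.
- Calls: one a week.
- Window: one session per call (the latest one), plus the time since it.

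**Per week.** With *s* sessions a week, the share of sessions outside the window is (*s* − 1)/*s*.

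- *s* = 5: 4/5 = 80%
- *s* = 4: 3/4 = 75%
- *s* = 3: 2/3 = 67%
- *s* = 2: 1/2 = 50%

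That gives 75–80% before surgery and 50–67% after. At two sessions a week it is exactly half, not a majority.

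**Whole programme with prehabilitation.** The share outside is 1 − (*p* + *r*)/(*p·a* + *r·b*). Over all combinations of the stated ranges:

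- Lowest: *p* = 1, *a* = 4, *r* = 6, *b* = 2. Sessions 4 + 12 = 16, calls 7, outside 9/16 = 56%.
- Highest: *p* = 4, *a* = 5, *r* = 5, *b* = 3. Sessions 20 + 15 = 35, calls 9, outside 26/35 = 74%.

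The lower bound does not come from the shortest programme (1×4 + 5×2 = 14 sessions, 6 calls, 8/14 = 57%). The longest programme (4×5 + 6×3 = 38 sessions, 10 calls) gives 28/38 = 74%.

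**Entry at T2 (rehabilitation only).** 10 sessions with 5 calls, or 12 with 6, give 50%. 15 sessions with 5 calls, or 18 with 6, give 67%.

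**What the visits add.** They have no stated recall limit, so every session is in principle covered by a later visit. By the legend to Fig. 1, the intervals are 1–4 weeks for T0–T1 and 5–6 weeks for T2–T3. Patients with a short time to surgery may have only T0 before it (Participant timeline {13}); their next visit is T2, although they also have few preoperative sessions.

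**After rewording.** If each call asks about all the time since the previous contact, the share of sessions outside the window is 0% at any training frequency.

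**The case against.** The strongest reply is that the visits already close the gap. The harms section says that all related events are recorded, both groups are asked in a standard way at every visit, and the calls are an addition. No session is outside adverse event capture altogether. This stands, and it limits the point to the calls and to the length of recall.

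Second, a reader might take 56–74% as the share of adverse events missed. The documents do not support that. An event from an earlier session that persists is still present in the time since the latest session and so falls within the question. Only events that began and fully resolved before the latest session are outside. The documents give no event rates from which to size that group.

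Third, a reader might infer that the training would look too safe relative to control. That does not follow either. Visits put the same question to both arms, while the calls go only to the exercise arm. The calls can therefore only add events in that arm, and any between-arm ascertainment difference they cause does not favour the training.

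Fourth, the phrase might mean the last *monitored* session, in which case the window would span the week. The text does not say so. If that was intended, the same rewording would make it plain.

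Fifth, the call is not the only source of safety information. The Discussion mentions regular monitoring of health status to adapt the exercise prescription, and {11b} lets a participant ask to stop at any time. This is fair, but neither passage describes a systematic question about events at each session.

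**Conclusion.** The point holds in a limited form. As written, the weekly call's window is shorter than the interval between calls, and 75–80% of preoperative and 50–67% of postoperative sessions lie outside it (56–74% over a programme with prehabilitation, 50–67% for entry at T2). The consequence is some risk of an absolute under-count of transient exercise-related events, and later information for the decisions in {11b}, because such events then depend on recall of up to 4 weeks or 5–6 weeks at visits.

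The figures assume one call a week, training at the prescribed frequency, and the literal reading of the question. If participants train less often than prescribed, the uncovered share falls.

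This is a minor matter of harms ascertainment. Nothing in the sample size, the primary analysis or the interim rule depends on it.

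**What to change.** In Adverse event reporting and harms {22}, and in the call script and adverse event form that follow from it, replace the closing phrase of the call question with *since the last contact (call or visit)*. Have the caller go through the exercise diary with the participant, and record the date of each event and the session it followed.

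The cost is one changed phrase and slightly longer calls. No extra calls, visits or staff are needed, and the intervention and the rules for changing or stopping it are untouched.
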